#### Questionnaires

The majority of the questionnaires to be used in the study are part of the routine evaluation of the PR programme. Patients will be given the questionnaires to fill in at home, following the initial assessment for PR. A week before the final discharge appointment, patients will be given (for those in the standard care group) or posted (for those on the web-based programme) the questionnaires once again to fill in at home and bring back when they attend for their final discharge appointment. Any additional measures used in the study (the EQ-5D-5L, a physical activity questionnaire, COPD Anxiety Questionnaire and a patient cost questionnaire) will only be given once the patient has consented to take part in the study.

#### Health status

Two disease specific questionnaires will be employed; the self-reported Chronic Respiratory Questionnaire (CRQ-SR) which has both an initial and follow-up version depending of time of administration^18^ and the COPD Assessment Tool (CAT).^19^ Self-efficacy will be measured using the PR Adapted Index of Self-Efficacy (PRAISE).^20^These measures are all part of the standard evaluation for PR. Participants to the study will additionally be asked to fill in the generic Euro-QOL(EQ-5D-5L).^21^

#### Anxiety and depression

The Hospital Anxiety and Depression Scale (HADS) is a simple self-reported measure that gives an indication of clinically important anxiety and depression.^22^ HADS is routinely used in the clinical evaluation of PR.

Participants will also be given the self-reported COPD Anxiety Questionnaire (CAQ) to complete before and after completing either rehabilitation programme. This questionnaire is currently being validated in English from the original German version.

#### Information needs

This will be assessed using the Bristol COPD Knowledge questionnaire (BCKQ).^23^ The BCKQ is routinely used in the clinical evaluation of PR. Patients randomised to the web-based PR programme will fill one of these out on line.

#### Patient cost questionnaire

A ‘patient cost’ questionnaire^24^ will be given to all study participants following consent. This questionnaire has been adapted for the study in order to determine costs to the patient and their family of the impact of the disease as well as any treatment they have needed for their COPD. The patient cost questionnaire will be administered again as part of the questionnaires given out prior to the discharge appointment.

#### Physical activity questionnaire

A physical activity questionnaire has been developed at UHL as part of this feasibility study. PACER (the Physical Activity Everday Recall) questionnaire has been designed to capture the everyday physical activities that people do on a regular basis. It asks people to estimate how much time they have spent doing a variety of day to day activities in the past 7 days. Participants will be asked to fill in the PACER questionnaire at the end of the week spent wearing the physical activity monitor. This will occur twice: prior to starting either programme of rehabilitation and again after the discharge assessment on completion of the assigned programme.

### Non-clinical study outcomes

#### Web-usage audit for the internet-based programme

Weekly and total web usage statistics for patients assigned to the web-based programme will be monitored as will the number and type of any technical problems that the project team or participants encounter.

#### Uptake and drop out

We will monitor the number of patients with COPD who are eligible to partake in the study as well as the number of those people who proceed to consent. We will also monitor the number of participants who start and complete rehabilitation in both treatment groups as well as the number of people who drop out. We will record how long it takes participants to complete the web-based programme and for those who drop out, a record of how soon they drop out and how much of the programme they have completed. This will enable us to identify if there is a particular point at which more people are likely to give up. Any serious adverse events will be reported to the sponsor and patients’ ability to exercise safely will be monitored.

#### Sample size estimation and recruitment target

The study will aim to recruit as many suitable patients as are referred to the PR service within the operational phase. One of the main objectives of this feasibility study is to provide data on recruitment and to enable an accurate estimation of sample size for a planned RCT. Based on calculations from previous studies carried out in the PR service, we anticipate a recruitment rate of around 100 patients during our operational phase. This feasibility study will enable us to estimate the required sample size for the subsequent RCT based on a realistic recruitment strategy.

#### Randomisation

Participants will be randomised into one of two groups: the intervention group who will take part in the web-based PR programme and the standard care group who will undertake conventional PR at the site they were referred to. Randomisation to treatment group allocation will be a 1:1 ratio to either group and will use internet based ‘Sealed Envelope’ randomisation codes where treatment group allocation is sent by automated email to the research physiotherapist.

#### Quantitative data analysis

As this is a feasibility study, it is not appropriate at this stage to have sufficient statistical power to detect pre to post rehabilitation or between treatment group changes. Therefore for the quantitative data, analysis will primarily be descriptive that is, estimation of means and SDs, proportion of patients eligible/willing to participate in the study. Primary outcome data (ie, the ISWT) will be used to estimate a sample size calculation and non-inferiority margin for a RCT. We will also collect data on drop out and completion rates for both programmes.

Data will be entered and stored on a secure web-based system, REDCAP, which has discrepancy management features. Data can be transferred from REDCAP to the Statistical Package for the Social Sciences (SPSS) for statistical analysis.

All patient information that is collected during the course of the research will be kept strictly confidential. With the patient's permission, their general practitioner (GP) will be informed of their participation in the study and that they may be contacted for relevant reports. Any information about the patient which leaves the hospital will have their name and address removed. Participants will not be identified in any subsequent written material. Results will be reported in such a way that completely preserves confidentiality.

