## Introduction

It is estimated that one in four people will develop chronic obstructive pulmonary disease (COPD) in their lifetime^1^ and it is the fourth leading cause of death in the UK. COPD is characterised by a progressive deterioration of debilitating symptoms and increasingly frequent exacerbations. Pulmonary Rehabilitation (PR) has been proven to be effective in improving quality of life, psychological functioning and physical activity and national guidelines recommend that PR should be available to all those who may benefit.^2^ However a survey by the British Lung foundation has found that fewer than 10% of people with COPD have access to such a service.^3^

The standard provision of PR is a supervised package of exercise and education, usually twice a week for a minimum of 6 weeks supported by a home exercise programme. However, some patients find visiting a hospital or community facility very difficult and many programmes report dropout rates as high as 50%. A web-based PR programme has the potential to be a novel and effective approach to increasing patient choice in the mode of delivery and setting of rehabilitation (especially to those patients who decline the offer of conventional PR) while simultaneously increasing the capacity of PR.

There is a growing evidence base for the use of the internet in the management of many chronic conditions in areas as diverse as the management of diabetes, Parkinson's disease, depression, rheumatoid arthritis, asthma, chronic pain and epilepsy.^4–10^ In COPD, Nguyen *et al*^11^ published pilot data on an online dyspnoea self-management programme which had comparable outcomes to a face to face programme but was stopped early due to multiple technical challenges with the online programme.

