### Outcome measures

#### Clinical measures

All the measures described below are routinely included in the clinical evaluation of our standard PR programme, with the exception of the use of activity monitors. All measures (except for activity monitors) will be completed at the time of initial assessment for PR by members of the rehabilitation team or at the consent appointment by the research team both who are experienced in these measures. The PR assessment includes information on medical history, medication and baseline demographic data. Standard measures of lung function, level of physical activity, exercise capacity, information needs and health status will be collected.

All measures will be repeated again at the discharge assessment following completion of either rehabilitation programme (usually approximately 6–7 weeks after starting the programme) and will be conducted by a research physiotherapist who will be blind to treatment group allocation.

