#### Primary outcome measure—exercise capacity

The primary outcome in any eventual trial is expected to be change in exercise capacity following rehabilitation, as measured by the Incremental Shuttle Walking Test (ISWT). The ISWT is a standardised, validated test^16^ of maximal performance and is used as a tool to prescribe the home walking programme. We will estimate a sample size for the subsequent RCT from the observed changes in ISWT in the feasibility study.

The Endurance Shuttle Walking Test (ESWT) will be used to measure endurance exercise capacity and the results of the test are expressed in seconds walked.^17^

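### The plan says this study's own ISWT data will be used to estimate the later RCT's non-inferiority margin, which those data cannot supply

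*Protocol article*

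**What the plan says.** The Quantitative data analysis section of the protocol article says: "Primary outcome data (ie, the ISWT) will be used to estimate a sample size calculation and non-inferiority margin for a RCT". One source, this study's ISWT data, is named for both quantities. No other section mentions the margin or gives it another basis, such as a minimal important difference, clinical or patient judgement, or external controlled evidence.

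The same paragraph says "it is not appropriate at this stage to have sufficient statistical power to detect pre to post rehabilitation or between treatment group changes". The Randomisation section describes a web-based PR arm and "the standard care group who will undertake conventional PR at the site they were referred to", so no arm goes without rehabilitation. On size, the plan says "we anticipate a recruitment rate of around 100 patients during our operational phase" and "Randomisation to treatment group allocation will be a 1:1 ratio to either group", which gives about 50 per arm. Follow-up is tied to finishing the programme: "All measures will be repeated again at the discharge assessment following completion of either rehabilitation programme".

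**The concern.** Two different things are asked of the same data. A sample size needs nuisance quantities (the SD of ISWT change, the baseline/follow-up correlation, attrition), and a pilot can estimate these. A margin is a judgement about how much of the benefit of conventional PR may be given up. It is bounded by how large that benefit is compared with no rehabilitation. A study with two rehabilitation arms does not observe that benefit.

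The margin decides whether the RCT may call the web programme non-inferior. If it follows the pilot's observed ISWT effects, it inherits their sampling error. A conventional arm that happens to gain a lot would produce a lenient margin, and one that happens to gain little would produce a strict margin and a much larger trial. Informing the design of that RCT is the stated aim of this study (Introduction), so the point concerns one of its main products.

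**Working it through.** The document states no margin, alpha, power, SD or expected ISWT change. The figure of about 100 is a recruitment forecast, so there is no stated calculation to reproduce. The check has two parts.

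**1. What the data contain.** There are two candidate quantities for a margin.

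- *Conventional-arm change from baseline to discharge.* It is uncontrolled, so it mixes the effect of PR with test learning and regression to the mean. Because follow-up is at discharge after completion, it also comes mainly from completers.
- *Between-arm difference.* This is what the RCT is meant to test. Deriving the margin from it would fit the criterion to an early look at the answer.

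Neither says what loss is acceptable.

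**2. How far a data-derived margin would move by chance.**

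Input from the document: about 100 patients at 1:1, so n = 50 per arm before dropout.

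Assumptions not in the document: true conventional-arm gain 50 m; SD of change 60 m; margin = half the observed gain; RCT with 90% power, one-sided 2.5% and true difference zero.

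- Standard error of the mean change: 60/√50 = 8.49 m.
- 95% range of the margin: 0.5 × (50 ± 1.96 × 8.49) = 25 ± 8.3, about 17 to 33 m.
- RCT size per arm: 2 × ((1.960 + 1.282) × 60 / margin)².
  - Margin 17 m: 2 × (194.5/17)² ≈ 262.
  - Margin 25 m: 2 × (194.5/25)² ≈ 122.
  - Margin 33 m: 2 × (194.5/33)² ≈ 70.
- Spread: 262/70 ≈ 3.7-fold.
- Between-arm difference, 95% half-width: 1.96 × 60 × √(2/50) = 23.5 m, about as large as the 25 m margin itself.

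Sensitivity to the assumed SD, still at 50 per arm: SD 50 gives 25 ± 6.9, or 18 to 32 m; SD 80 gives 25 ± 11.1, or 14 to 36 m.

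Sensitivity to dropout: with 25 completers per arm and SD 60, the margin range is 25 ± 0.5 × 1.96 × 60/√25 = 25 ± 11.8, about 13 to 37 m. The RCT size then runs from 448 to 56 per arm.

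**3. The same check in SD units, comparing the two approaches.** Assumptions: 80% power, one-sided 2.5%, true difference zero, true gain 0.75 SD, 50 per arm.

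| How the margin is set | Margin | RCT n per arm |
|---|---|---|
| Half the observed gain | 0.24 to 0.51 SD | 281 down to 60 |
| Fixed externally at 0.375 SD, only the SD taken from the pilot | does not move | 83 to 145 |

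At the true values both approaches give 112 per arm. In the second row only the sample size carries pilot error; the non-inferiority criterion carries none.

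**The case against.** The strongest reply is that "Primary outcome data (ie, the ISWT) will be used to estimate a sample size calculation and non-inferiority margin for a RCT" need not be exclusive. The article condenses a fuller document, the aim is to inform an RCT design, and the section on conventional PR cites an evidence base for the local programme. The authors may intend to combine that evidence with the pilot data. This softens the point but does not remove it: the sentence gives margin and sample size the same single source, and nothing elsewhere gives the margin another. It is a stated method, so it cannot be put down to detail left out of an article.

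Other parts of the reply stand, and they limit the point.

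- A reader might infer that the margin would be chosen after the results it is meant to judge. The text does not support that. A margin set after the pilot and before the RCT is still prespecified for the RCT.
- A reader might take the eight-fold spread at 25 per arm (448 to 56) as the expected size. It relies on the remark that "many programmes report dropout rates as high as 50" per cent, an upper background figure for other programmes in the Introduction and not a planning assumption here.
- The half-the-gain rule, the 50 m and the 60 m are all assumed. The document states no rule for deriving a margin. Nor does it show that any of the RCT sizes above would be infeasible.
- The primary outcome section might be read as repeating the error: "We will estimate a sample size for the subsequent RCT from the observed changes in ISWT in the feasibility study". It concerns sample size only, for which ISWT variability is a legitimate input, so it is not a second instance.

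**Conclusion.** The point holds. The plan names this study's ISWT data as the source of the RCT's non-inferiority margin, and a study with two active arms and no claimed power cannot provide one. That conclusion follows from the design and needs no numerical assumption.

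The size is illustrative. Under the assumptions listed, with 50 per arm and no dropout, chance would move the margin roughly two-fold (33/17 ≈ 1.9) and the RCT size nearly four-fold, and dropout would widen both.

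Severity is moderate. A reader might infer that the feasibility study itself is compromised, but its analysis is mainly descriptive, no margin is applied in it, and none of its procedures or estimates changes. The harm arises if the later RCT adopts a pilot-derived margin without independent justification.

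**What to change.** In the Quantitative data analysis section, delete the reference to the non-inferiority margin, so that the sentence promises only a sample size estimate, as the study objectives and the primary outcome section already do. Add one sentence saying that the margin will be justified independently of the ISWT effects observed in this study and fixed before the RCT starts. Its basis should be a clinically important ISWT difference and external controlled evidence of PR against no rehabilitation, with clinical agreement and that of the existing patient and public involvement group.

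State what the pilot does supply: the SD of ISWT change, the baseline/follow-up correlation, attrition and recruitment. The observed conventional-arm gain may serve at most as a plausibility check on the externally justified margin.

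The cost is one or two sentences here and a short margin justification for the RCT protocol. No patients, visits or procedures are affected.

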### Health economic evaluation

As part of the feasibility study, we aim to test the methods to be used in the proposed economic evaluation of the subsequent RCT. The perspective of the economic analysis will be that of the NHS and personal social service. Costs to be obtained will include the costs of providing web-based and the conventional rehabilitation programme. We will also test the validity and feasibility of administering the ‘Patient Cost Questionnaire’^24^ as well as the EQ-5D-5L for any future economic evaluation. The economic analysis will aim to examine the response rates, sample size calculation and other necessary information to calculate the cost savings for future economic evaluation.

### Qualitative research

The aim of the qualitative research is to identify possible barriers and facilitators to participation in a trial and in the web-based PR programme, in order to maximise chances of avoiding recruitment and retention problems during the eventual RCT and to help plan qualitative work that can contribute to a prospective process evaluation during the eventual trial.

We will invite patients to take part in a semistructured interview following their discharge assessment. We aim to conduct the interviews with a purposive sample of a wide range of participants including those who took part in the web-based rehabilitation programme as well as, if possible, with those people who dropped out.

The topic guide has been designed by a health psychologist in collaboration with our departmental PPI Advisory group to cover views of recruitment, randomisation, ongoing participation, completing the battery of assessments and any factors that may help or hinder participation in research and/or doing the rehabilitation programme such as support from family members etc. The interviews will be conducted by a health psychologist experienced in conducting qualitative research and will take place either at the hospital or in the patient's home as preferred.

#### Qualitative data analysis

Analysis will be via techniques based on a grounded theory approach.^25^ This is a data driven approach in which the researcher attempts to use the data to build a theory, while doing everything possible to ‘test’ the theory in the process. In the context of this feasibility study it would mean building a set of ideas about what could help, or get in the way of optimal recruitment and retention, with ways of testing emerging understanding as the qualitative component proceeds.

#### Qualitative methods

Analysis will involve audio recording of interviews (with informed consent) and verbatim transcription, then a team approach to a process known as constant comparison in which scrutiny of a small number of divergent transcripts gives rise to an initial coding frame (a set of categories of barriers and facilitators, for instance). The initial coding frame is then applied to subsequent transcripts, and if new data contradict the coding frame, the latter is revised and further data collection will confirm or disconfirm the model. At the end of this process the researcher has a coding frame that ‘fits’ the data (rather than trying to make the data ‘fit’ the coding frame). The findings would therefore be a set of issues that can help/hinder recruitment and retention, that could inform a subsequent trial.

### Ethics and dissemination

The findings from this feasibility study, particularly in relation to patient preferences and acceptability, will inform the design of any subsequent RCT. In the longer term we will seek to implement the findings of the RCT into daily practice and locally we will share the results of the feasibility study with local primary and secondary care interface groups, such as commissioning teams and service managers. We also aim to invite a local COPD commissioner to be a co-applicant for the full RCT and to sit on the study steering group. The steering group meets every 6 months to audit the trial conduct.

We have a number of international and national visitors who come to share our practice which we anticipate will stimulate interest in the study findings. We will be able to use the internet to widely publicise the findings of our work and promote interest in the internet-based programme.

We have a Pulmonary and Cardiac Rehabilitation PPI Advisory group whose members are current and ex-pulmonary and CR patients or interested members of the public who have participated in previous research trials. A strategy for disseminating the results will be coordinated through this group and the study steering group.

The results of this feasibility study will be presented at appropriate national, international and regional respiratory and physiotherapy conferences, local study days in primary and secondary care as well as through peer reviewed journals.
